## Discussion

This protocol describes a RE of a home-based PC program for non-cancer patients in Singapore. RE is adopted to provide an in-depth understanding about whether the program works, for whom and in what circumstances. This study carries significant implications for various stakeholders. For the program, the study will generate new insights about the implementation, effectiveness of the program and explicit context-specific recommendations. By understanding what works and does not work, relevant stakeholders can refine program components and focus resources to ensure effectiveness of the program. Information on whom ViP works will help to refine selection criteria. Meanwhile, insights on mechanisms and contextual influence on ViP may be useful in informing required adaptations in the program strategies.

For policy makers, findings from the study will inform the potential of generalist involvement in home-based PC and policy-relevant insights for future enhancement of PC to support the aging population. Globally, most prior evaluations of home PC programs [11,39,40,41,42] focused mainly on assessing the effectiveness with limited information on the implementation processes. Also, few of these prior studies reported the use of RE approach. This study findings can be used to illustrate the applicability/suitability of the realist approach in the field of PC.

## Strengths and Limitations

The RE approach adopted in this study provides a useful guiding framework for a comprehensive evaluation of ViP. It is well fitted as RE seeks to answer relevant questions of interest, is flexible and able to accommodate changes surrounding interventions implemented in real-world setting. Moreover, the use of mixed methods allow us to draw on the strengths of both qualitative and quantitative methods, enhancing the credibility of the evaluation findings and allows for generation of in-depth insights.

With this evaluation approach, evaluators work closely with the key stakeholders (program designers, implementers, patients and caregivers) throughout the evaluation journey to co-define evaluation objectives, IPT, identify constraints to the feasibility of implementation of the evaluation itself, collect data, interpret findings and refine program theories. This provides confidence on the relevance of the evaluation efforts and likelihood for adoption of recommendations to improve relevant components of ViP and/or define future PC models.

Nevertheless, RE approach and mixed methods design are relatively new in comparison to the positivist approach commonly used in the evaluation of medical interventions. This may draw criticism for not being as rigorous as the typical RCT due to the lack of knowledge on the utility of this niche approach. Furthermore, we acknowledge that the use of mixed methods design also increases complexity. We strive to reach optimal integration of data at multiple levels – study design, methods, interpretation and reporting – using the convergent parallel mixed methods approach which connects and merges methods and findings [38].

Furthermore, as participation in the evaluation efforts is voluntary, we also recognize that selection bias may be introduced in this study. To account for selection bias, demographic information including age, gender, ethnicity and role (for healthcare providers) are collected and will be compared between study participants and those who declined to participate. Given the sensitivity around the topic of PC and prospective data collection methods, difficulties in recruitment and follow-up with respondents are also anticipated. In order to maximize recruitment numbers, evaluators will work closely with main care providers to obtain “buy-in”. If necessary, the recruitment period will also be extended to allow more people to participate. To minimize the numbers lost to follow-up, research appointments are scheduled at participants’ time and place of convenience in collaboration with participants’ healthcare provider. Where loss to follow-up inevitable due to death, survival analysis will be conducted to account for the missing data.

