3	% of needy patients who were provided support	Administrative database & interviews with caregivers	Quarterly for the first 2 years of the programme					Change in caregiver burden score before and after intervention	Zarit Burden Interview-12	Baseline (at enrolment) and every 3 months after enrolmentuntil patients’ death	

								No. of ED attendances, in-patient admission and length of stay (LOS)	Administrative databases	1 month (30 days), 3 months (90 days) and 6 months (180 days) prior to death	

								% of patients with good management of symptoms	PCOC – symptoms assessment		
	
4	% of cases discussed in the MDM (multidisciplinary meetings)	Administrative database		Providers’ working experience	Interviews with providers	At least 6 months after program implementation		Development costs, program implementation costs and healthcare utilization costs	Administrative database	6 months prior to death	
		
	Quality of collaborative and communications between providers	Interviews with providers						Average duration in each PCOC stage		1 month (30 days), 3 months (90 days) and 6 months (180 days) prior to death	
	
5	Implementation experience	Interviews with providers	At least 6 months after program implementation					Perceived quality of care	Mortality follow-back survey	≤3 months after death	
	
*6*	Extent of support from management							Sustainability	Clinical Sustainability Assessment Tool (CSAT)	At least 6 months after program implementation	

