#### Study participants

Two distinct groups of study participants – healthcare providers/managers and healthcare users will be recruited into this study. Healthcare providers/managers who are involved in the implementation of ViP will be invited to participate in the interviews through emails. Healthcare users will be recruited through ViP team/physicians in-charge and/or home care nurses.

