#### Data Collection

Context, mechanisms and relationships between context and outcomes, as defined in phase 1, will be tested through interviews with healthcare providers and users. As suggested by Manzano [29], questions to be asked in these interviews aim to ascertained how the program works, for whom, in what circumstances and how implementation has veered from what was initially planned. A purposive sample of 15 healthcare providers/managers and 15 healthcare users (patient and/or carers) per disease condition will be invited to take part in face-to-face or virtual interviews. The eventual sample size will be determined based on thematic saturation of the study. Data saturation is reached when the ability to obtain additional new information has been attained, and when further coding is no longer feasible [30].

In ensuring the quality of data collected, an interview guide will be used and interviewers will routinely reflect on interview experience and discuss data as they are being collected. Based on emerging understanding and identification of key knowledge gaps throughout the process of interviewing, interview questions will be revised accordingly.

Healthcare services utilization, health outcomes, healthcare cost and caregiver burden data will be collected and analyzed over time to evaluate intervention outcomes of ViP. A quasi-experimental design will be adopted by comparing the outcomes of the intervention group against a comparator group for healthcare utilization, outcomes and cost. Due to limited data available, a pre-post comparison will be made for caregiver burden. A quasi-experimental design is selected as it more truly mimics real-world constraints and provide a balance between internal and external validity [31]. Pragmatically, all patients who agree to participate, are accepted into the home-based PC service, utilized the services for at least one month and passed away as of December 2022 will be included as the intervention group. A retrospective comparator group will be identified from available CGH and SACH clinical databases. We plan to restrict the databases to within CGH and SACH for the identification of comparators. This is because patients are planned to be recruited from CGH and SACH in the first 2 years. This is a way of ensuring comparability between intervention and comparator group while keeping the data manageable.

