Data for both intervention and comparator group will be extracted from SingHealth-iHiS Electronic Health Intelligence System (eHints), a common database of patient level data across all SingHealth institutions. Development and implementation cost will be extracted from ViP program database and potentially finance department. For comprehensiveness, we may also merge dataset with data held by the Ministry of Health to obtain nationwide acute hospital utilization (ED visits, hospital admissions, ICU utilizations, length of stay and date of death) using National Registration Identification Card (NRIC) of subjects included in the study.

Primary informal caregivers of ViP patients will be invited to complete a Zarit Burden Interview (ZBI) – 12 items to assess caregiver burden at enrolment and every 3 months after enrolment until patients’ death. The ZBI is a widely used tool for assessing caregiver burden among those who provide care for patients with various illnesses, including those at the end-of-life [34,35]. A higher score on the ZBI represents higher burden. As suggested by Stagg and Larner, a score of “0–20”, “21–40” and “>40” will be considered as little or no, mild/moderate and high caregiver burden respectively [36].

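### Comparing participants with decliners on demographics cannot account for selection bias: it misses selection in who is approached, does not see illness course, and adjusts nothing

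*Protocol article*

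**What the plan says.** Under Strengths and Limitations, the article gives one source of selection: "as participation in the evaluation efforts is voluntary, we also recognize that selection bias may be introduced in this study". The remedy, presented as the way to account for that bias, is that "demographic information including age, gender, ethnicity and role (for healthcare providers) are collected and will be compared between study participants and those who declined". The list of variables is open-ended, but only within demographic information, and role applies to providers. For patients and carers the named variables are therefore age, gender and ethnicity.

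The Study participants section gives the route by which users enter: "Healthcare users will be recruited through ViP team/physicians in-charge and/or home care nurses". The limitations section relies on the same staff to raise recruitment: "evaluators will work closely with main care providers to obtain" their support.

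Two quantitative user-reported outcomes depend on agreement. "Perceived quality of care" comes from a mortality follow-back survey within three months of death (Table 2, theory 5). For burden, "Primary informal caregivers of ViP patients will be invited to complete a Zarit Burden Interview" at enrolment and every three months until death (Data Collection).

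**The concern.** A check on selection has to compare the people studied with the people they are meant to represent, on characteristics related to the outcome. This one falls short in three ways.

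- **Comparison group.** A user must be approached before they can decline. Selection at the approach step lies outside the comparison.
- **Variables.** Age, gender and ethnicity need not track diagnosis, instability, late admissions or place of death, which could plausibly affect both willingness to take part and the rating given.
- **Purpose.** A table of differences describes selection. No adjustment is attached to it.

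What is at stake is how far the follow-back survey can be read as the experience of ViP families in general. A balanced demographic table would be taken as reassurance that it cannot give.

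**Working it through.** The article states no figure here, so there is nothing to reproduce. The check has two parts.

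**1. Does another stated safeguard cover the gap?**
- Propensity matching uses functional status, clinical status and re-admission, but it balances ViP patients against the retrospective comparator, not participants against non-participants.
- Survival analysis is offered for loss to follow-up through death, which occurs after recruitment.
- The sensitivity analysis under Data Analysis is not tied to selection.

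None covers it.

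**2. What would the planned comparison show if selection were present?** Every input here is an assumption; none comes from the documents.
- s = share of enrolees with a poor course: 30% (range 20–40%).
- Other families: approached at 90%, agree at 70%.
- Poor-course families: approached with probability a, agree with probability g.
- Demographics unrelated to course.

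Poor-course share among:
- participants = s·a·g / [s·a·g + (1−s)·0.9·0.7]
- decliners = s·a·(1−g) / [s·a·(1−g) + (1−s)·0.9·0.3]
- never approached = s(1−a) / [s(1−a) + (1−s)·0.1]

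Selective approach only (s = 0.30, a = 0.60, g = 0.70):
- participants: 0.126 / (0.126 + 0.441) = 22%
- decliners: 0.054 / (0.054 + 0.189) = 22%
- never approached: 0.12 / (0.12 + 0.07) = 63%

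Selective refusal only (s = 0.30, a = 0.90, g = 0.40):
- participants: 0.108 / (0.108 + 0.441) = 20%
- decliners: 0.162 / (0.162 + 0.189) = 46%

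| Scenario, s = 30% | Participants | Decliners | Never approached |
|---|---|---|---|
| No selection (a = 0.90, g = 0.70) | 30% | 30% | 30% |
| Approach only, a = 0.60 | 22% | 22% | 63% |
| Approach only, a = 0.30 | 12.5% | 12.5% | 75% |
| Refusal only, g = 0.40 | 20% | 46% | 30% |

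For s from 20% to 40%, the participant share is 14–31% when a = 0.60 and 8–18% when a = 0.30, with g = 0.70.

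Under selective approach, participants and decliners have the same make-up, so no variable would reveal a difference between them. Under selective refusal the difference is large, but a demographic table is expected to show none.

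**Effect on a survey percentage.** Suppose 85% of other families and 60% of poor-course families would rate care as good. The overstatement is (s − participant share) × 0.25:
- approach only, a = 0.60: (0.300 − 0.222) × 0.25 = 1.9 points
- approach only, a = 0.30: (0.300 − 0.125) × 0.25 = 4.4 points
- refusal only: (0.300 − 0.197) × 0.25 = 2.6 points
- both, at the extreme tried (s = 0.40, a = 0.30, g = 0.40): (0.400 − 0.113) × 0.25 = 7.2 points
- no selection: 0

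**The case against.** The strongest reply is that selective non-approach is conjecture. No section says that invitations are discretionary, or that the care team is the only route. The follow-back survey's own invitation procedure is not described, so applying the general user route to it is an inference. Table 2's outcome sample-size entry, year 1 and 2 enrolees, may extend down the column, in which case all enrolees are already the intended frame. Approach logs are also a detail that an article may leave to the full protocol. This stands as a limit: the risk is structural, not demonstrated. It does not rescue the check, because the article states a specific remedy and its purpose, and that remedy cannot do what is claimed. If all enrolees are the intended frame, they are also the right comparison group.

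Several stronger readings are tempting, and the documents do not support them:
- *Families with the worst course are invisible.* Those approached who decline do enter the comparison; only their course is unseen.
- *Caregiver burden will look better than it is.* The first ZBI-12 invitation comes at enrolment, so a later difficult death cannot influence it. The analysis is of before-after change, and a biased level does not imply a biased change.
- *The interviews are compromised.* They are purposive, set per disease condition and continued to saturation; representativeness is not their aim.
- *The evaluation loses the cases that show for whom ViP fails.* Dropout, timeliness and responsiveness come from administrative data on year 1 and 2 enrolees and do not depend on invitation.

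**Conclusion.** The point holds in limited form. The stated comparison cannot detect selection in who is approached, cannot show differences in illness course between participants and decliners, and describes selection without adjusting for it. It matters mainly for the follow-back survey of perceived quality of care and to a lesser degree for the ZBI-12 sample. It does not apply to the purposive interviews or to the administrative indicators on all enrolees.

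Its size is unknown. The 0 to 7 point range comes entirely from assumed approach rates, agreement rates and ratings, and is zero if poor-course families are approached and agree as often as others. What needs no assumption is that the check as written would give no warning of selection in who is approached. The authors do acknowledge selection bias, so the correction concerns the remedy and the claim made for it.

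**What to change.** 1. Log the numbers enrolled, approached, agreed and declined, separately for the follow-back survey and the ZBI-12.
2. Compare participants with all eligible ViP enrolees (for the follow-back survey, those who have died). Besides demographics, use primary diagnosis, last PCOC stage, specialist or generalist tier, time from enrolment to death, acute admission in the last 30 days and place of death. Variables that need a date of death apply only to those who died.
3. Where the groups differ, weight the survey and ZBI-12 results to all enrolees as a sensitivity analysis. State the assumption: given the weighting variables, those who did not take part would have answered like those who did.
4. For the unweighted comparison, change the wording from *account for* selection bias to *describe* it.

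The programme already generates or plans to extract these variables (referral diagnosis, PCOC assessment at each contact, care tier, utilisation before death, place of death), so the cost is wording, a simple log and some extra analysis. Ethics cover for using programme data on people who did not take part must be confirmed. The invitation route can stay as it is: having evaluators contact bereaved families directly would be a new procedure with consent and privacy implications, and the comparison can be repaired without it.

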## Data Analysis

Interviews will be transcribed verbatim and each transcript will be checked against recordings for accuracy. Interview transcripts and observation notes will be coded using NVivo. Interviews conducted in languages other than English will be translated and transcribed in English. Like phase 1, interview transcripts will be coded and analyzed by 2 evaluators using NVivo as suggested by Gilmore et al [28]. To ensure the rigor of data analysis, regular meetings will be planned among evaluators to discuss the emerging themes identified in the data. In addition, re-analysis of qualitative data will be conducted if discrepancy is identified. An objective third person will be called in if the discrepancy cannot be resolved between the two evaluators.

Quantitative data analysis will be conducted using STATA. First, univariate analysis will be conducted using chi-square for categorical variables and t-test/ANOVA for continuous variables. Then, to estimate the effect of the program on the outcome of interest, multivariable regression analysis (Poisson or Negative Binominal regression) will be used for count data and generalized linear models will be used for continuous data. For dichotomous outcome variables, logistic regression will be used. Subgroup analysis may be conducted by patients’ primary conditions to allow for the detection of differential effects of ViP on various disease groups. To ensure robustness of the analysis, sensitivity analysis will also be performed.

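### Survival analysis is named to handle data missing through death, but the outcome that death cuts short is a repeated caregiver burden score, on which it cannot act

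*Protocol article*

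**What the plan says.** The Strengths and Limitations section expects difficulty in following respondents and then commits to a method: "Where loss to follow-up inevitable due to death, survival analysis will be conducted to account for the missing data".

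The Data Collection section has primary informal caregivers complete the ZBI-12 "to assess caregiver burden at enrolment and every 3 months after enrolment until patients’ death". The data framework (Table 2, under Study Design) defines the outcome as "Change in caregiver burden score before and after intervention". On design, Data Collection says: "Due to limited data available, a pre-post comparison will be made for caregiver burden".

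The Data Analysis section says that "univariate analysis will be conducted using chi-square for categorical variables and t-test/ANOVA for continuous variables", and that in the multivariable step "generalized linear models will be used for continuous data". It does not say whether the t-test is paired, and it names no method for repeated scores from the same caregiver.

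**The concern.** Survival analysis answers how long until an event. A change in a burden score asks how a mean moves over time. Once the patient has died, no further ZBI score under the patient's care exists, and a hazard or a survival curve does not supply one or correct a mean for its absence.

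Reducing caregiver burden is one of ViP's five stated aims and an outcome of the third initial program theory in Table 1. It is assessed with no control group, so selective loss of caregivers cannot cancel between arms. If the named method does nothing, the default is a before-after comparison in caregivers whose patients lived long enough to yield a second score. That result could be read as an effect of the programme on all enrolled families.

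**Working it through.** The article gives no sample size, effect size, SD, survival distribution or within-caregiver correlation for the ZBI, so there is no figure to reproduce. The check has three steps.

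**Step 1. Which outcome does the sentence reach?**
- Utilization and health outcomes are anchored at the date of death and counted back 30, 90 and 180 days; utilization cost covers the six months before death (Data Collection). Death does not make these missing.
- Perceived quality of care comes from a survey after death (Table 2).
- Time in each PCOC stage is a duration, but Table 2 reports it as an average in windows before death, not as a time-to-event endpoint.
- The ZBI-12 is scheduled forward from enrolment and ends at death. It is the repeated score that death interrupts.

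**Step 2. How many caregivers would have no post-baseline score?**
Inputs from the article: first post-baseline ZBI at 3 months; referral prognosis under 12 months, or under 6 for other frailty. Assumption: exponential survival from enrolment with median m months.
- No post-baseline score: P(T < 3) = 1 − 0.5^(3/m).
- The same among patients with at least one month of service: P(T < 3 | T ≥ 1) = 1 − 0.5^(2/m).

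| Assumed median m (months) | No post-baseline ZBI | Given ≥ 1 month of service |
|---|---|---|
| 2 | 65% | 50% |
| 3 | 50% | 37% |
| 6 | 29% | 21% |
| 9 | 21% | 14% |
| 12 | 16% | 11% |

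The last column matters only if the one-month service rule for the intervention group also applies to the ZBI, which the article does not say.

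**Step 3. Does leaving these caregivers out distort the change?**
A simulation with assumed values: 100 caregivers, ZBI mean 20, SD 8, true change zero, visits at 0, 3, 6 and 9 months, within-caregiver correlation 0.5 or 0.7, 300 runs per setting. Death after each visit depended on the last observed score, with log-odds 0, 0.5 or 1.0 per SD. About 62% to 65% of patients remained at 3 months.

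| Analysis | Death unrelated to burden | Death related to observed burden |
|---|---|---|
| Paired t-test at 3 months, mean change | about 0 | +0.5 to +1.3 points |
| Paired t-test, false rejection at nominal 5% | 4% to 6% | 10% to 24% |
| Mixed model with caregiver random intercept, slope per visit | +0.01 to +0.03 | −0.02 to +0.03 |
| Mixed model, false rejection | 6% to 7% | 3% to 6% |

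The Monte Carlo standard error of a 5% rejection rate with 300 runs is √(0.05 × 0.95 / 300) = 1.3 percentage points, so the mixed-model rates are compatible with 5%. The paired bias is 0.5/8 = 0.06 to 1.3/8 = 0.16 SD. It arises because caregivers who stay have baseline scores that are low partly by chance and then drift back up. It would change sign if lower burden went with earlier death.

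**The target matters.** At correlation 0.5 and log-odds 0.5 per SD, mean burden among caregivers of patients still alive fell by 1.9 points by the fourth visit. A GLM by visit estimated −1.84 and the mixed model −0.13. Each is right for a different question: the GLM for the mean among those still alive, the mixed model for the mean as if no series had been cut short.

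**The case against.** The strongest defence is that a condensed article leaves correlation structure and missing-data detail to an analysis plan. That stands for the Data Analysis section. It does not save the sentence on survival analysis, which commits to a method for this problem. Survival analysis could be one component of a joint model of burden and time to death, but no such model is described.

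Two stronger readings are tempting, and the article supports neither.
- **That the Data Analysis section prescribes an independent-observations analysis with wrong standard errors.** It says neither unpaired nor independent. A pre-post change is naturally tested with a paired t-test, which handles the correlation. The two harms also need opposite analyses: caregivers without a second score drop out of a paired test, while the standard error is wrong only in an unpaired one.
- **That there is nothing to censor because every analysed patient has died.** The intervention group for the matched comparison is limited to patients who "utilized the services for at least one month and passed away as of December 2022 will be included as the intervention group". The ZBI is offered to caregivers of ViP patients without that limit, and patients can leave the service alive.

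It is also fair to say that the size is uncertain. The background section notes that non-cancer patients often outlive their prognosis, which favours the longer medians and the lower percentages. If death is unrelated to burden, the paired estimate is unbiased.

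**Conclusion.** The point holds for the sentence in Strengths and Limitations: survival analysis cannot account for ZBI scores missing through death, and no time-to-event endpoint is defined to which it could apply. That conclusion needs no numerical assumption.

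The size does. The share of caregivers with no post-baseline score is about 65% to 16% for assumed exponential medians of 2 to 12 months. The bias of a simple paired comparison, +0.5 to +1.3 points on an assumed SD of 8, arises only if early death is related to burden. The utilization and cost comparisons with the matched group are not affected. The burden result should be corrected because, as planned, it is unclear to whom the estimated change applies.

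**What to change.** Replace the survival-analysis sentence with a repeated-measures analysis of all available ZBI scores that accounts for within-caregiver correlation. State one estimand and the model that matches it:
- **Mean trajectory as if follow-up were not cut short by death:** a linear mixed model with a caregiver random intercept, assuming that death depends only on observed scores; or
- **Mean burden among caregivers of patients still alive at each visit:** a GLM, or GEE with an independence working correlation, with standard errors clustered by caregiver.

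As sensitivity analysis, fit a joint model of ZBI and time to death, or analyse ZBI on a time scale counted back from death. Report how many caregivers have no post-baseline score and compare their baseline scores with those of the others.

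The cost is a few sentences and some analysis time, with no new data. The mixed model rests on an untestable assumption and would not remove bias if death depended on unobserved burden, which is why the sensitivity analysis is needed. An additional earlier ZBI would be an optional change to data collection in an ongoing evaluation and is not part of this correction.
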